#### Primary outcomes

##### BMI z-score (main study)

Fasting body weight and height are measured in duplicate to the nearest 0.1 kg and 0.1 cm, respectively, using a combined calibrated digital scale and stadiometer (Seca 285, Seca GmbH & Co. KG, Hamburg, Germany), with the children wearing underwear and a poncho (the weight of the poncho is known and subtracted). BMI (weight/height^2^) will be calculated, and normative age- and sex-specific reference data will be used to calculate the BMI z-score (37); using the WHO Anthroplus software for children aged 5–19 years.

##### Learning ability (main study)

The assessment of learning ability will be performed as motor skill learning and wordlist memory, involving implicit and explicit memory processes (38, 39). Motor skill learning is assessed using a computer-based sequential visuomotor task that requires both speed and accuracy. The children track visually displayed targets on a 24-inch computer screen placed in front of them by controlling the vertical position of a cursor using dynamic finger pinching movements (40s) (40–42). During the task, each target is displayed for 2s, and performance is calculated as a percentage of time on target score across all displayed targets. The task will involve the dominant hand determined by handedness preference.

After introduction to the task and a standardized familiarization procedure (1 min), the child will perform a baseline test (105 s), followed by four practice blocks of 2 min each, and then retention tests (immediate and 24 h later). Baseline and retention tests are identical. The test will assess overall 24 h learning, defined as the difference between the performance (percentage score out of 100) at baseline (day 1) and a delayed retention test 24 h later (day 2). This will be compared before and after the intervention. Performance will also be assessed immediately after the learning session to distinguish within-day from between-day (overnight) learning effects in secondary analyses (38, 39). Additionally, participants will perform a non-sequential variant of the motor task at delayed retention, enabling the distinction of sequence-specific and more general motor learning in secondary analyses. The procedure is identical at visits A and B. For both groups, we expect a repeated administration effect at visit B, but the learning task has not demonstrated ceiling effects in previous studies, meaning that repeated testing is feasible.

Explicit memory will be assessed using a word memory test with encoding in the main experiment and assessment with 2-min and 24-hour delayed recall. The encoding phase involves a 2-min period during which 20 words are displayed on a screen and read aloud in an automatized procedure. Explicit memory is assessed as the number of correctly recalled words (during 2 min) at delayed recall, i.e., total within and between session effect (range: from 0 to 20). All words are common nouns, and all words are replaced between visit A and visit B.

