### Data collection and outcomes

The study involves various visits for participating families, including an information meeting, screening, assessment visits A and B (each spanning over 2 days), visit C, sessions with the family advisor, and additional visits for those participating in substudy-I and substudy-II. Data collection follows standard operating procedures and is detailed in Tables 1, 2. Most data are collected during the active intervention period. Participants who discontinue the intervention will be invited to attend an early termination visit. Participants who withdraw from the study during the active intervention will be invited to attend an early termination visit identical to Visit B, whereas those who withdraw during follow-up will be invited to attend a visit identical to Visit C.

**Table 1 T1:** Overview of visits and assessments for the main study.

Method/assessment	Outcomes	At home	Visit A	At home	Visit B	At home	Visit C
		(Week −1)	(Week 0)	(Weeks 1–11)	(Week 12)	(Weeks 13–37)	(Week 38)
Method/assessment	Outcomes						
Anthropometry and metabolic health							
Anthropometric measurements	BMI z-score		X		X		X
DXA	Fat and lean mass and fat percentage, BMD, and BMC		X		X		X
Fasting blood sample	Clinical biochemistry: cardiometabolic risk factors, appetite-regulating hormones, sex hormones, and PBMCs.		X		X		
Puberty status	Tanner stage		X		X		X
Sleep							
Actigraphy	Sleep duration, movements, and awakenings	X		X		X	
Polysomnography	Sleep stages, duration, latency, awakenings, and arousals		X		X		
Stanford Sleepiness Scale	Alertness		X		X		X
Sleep Screen Questionnaire-Children and Adolescents (SSQ-CA)	Sleep duration, latency, awakenings, and tiredness/sleepiness		X		X		X
Learning and brain function							
Track-It and word memory test	Learning ability, including skill learning ability and explicit memory		X		X		
EEG/EMG	Muscle activity during skill learning, corticocortical functional connectivity, and corticomuscular connectivity		X		X		
School performance	Mathematics proficiency and Danish reading comprehension		X		X		X
Motor skills							
Pegboard test and handgrip dynamometer	Fine motor skills and muscular strength (gross motor skills)		X		X		X
Lifestyle behaviors							
3-day dietary record	Total energy intake, energy percentage of carbohydrate, fat, protein, and fiber, and meal timing	X		X		X	
Meal timing diary	Eating window duration	X		X		X	
Actigraphy	Total physical activity and time spent on MVPA	X		X		X	

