### Sample size determination

Sample size calculations were designed to achieve 80% statistical power (corresponding to a type II error of 0.2). Two-sided hypothesis testing with a type I error rate of 2.5% (i.e., *P* ≤ 0.025) was chosen because there are two co-primary outcomes, and a 20% dropout rate over 12 weeks was assumed.

A previous study on sleep extension in children aimed for moderate-to-large effect sizes, Cohen's *d* = 0.58, based on preliminary data (21). This study aims to achieve a similar effect size, resulting in an absolute difference in the final BMI z-score of 0.52 units between groups. We consider this effect size to be appropriate and clinically relevant, as studies of lifestyle interventions in children have demonstrated important clinical benefits with decreases in BMI z-score of 0.25–0.50 units (73).

In a previous study of sleep extension in children, including children of any weight status, a mean BMI z-score of 0.9 was reported, with a standard deviation of 0.9 (21). Based on these data, we assume a mean baseline BMI z-score of +1.0. Under these assumptions, we estimate we will need 114 children assigned in a 1:1 ratio between the active and control groups to detect an effect size of d = 0.58. Although sleep intervention studies in children report dropout rates below 4% (21), we based our calculations on a more conservative 20% attrition rate (i.e., five times higher than previously observed but more realistic for our longer study duration and more demanding assessment). We estimated that we would need to enroll 142 children (for 114 completers).

Considering learning and memory, we defined our co-primary outcome as overall 24 h learning. Previous studies on sleep extension in children have found moderate effect sizes for improved performance in the cognitive domain, corresponding to similar effect sizes for the academic performance domain (31). We have not found studies investigating the effects of sleep or sleep extension on 24 h learning effects. In recent experiments, we found that overnight sleep is related to total 24 h skill learning in children and that children benefit from offline learning effects compared to adolescents and young adults (41). Based on the mean performance and standard deviation at baseline among school-aged children aged 8–10 years, we anticipate that a sample size of 142 will allow us to detect a moderate-to-large effect size in the learning and memory domain at *P* ≤ 0.025, with 80% power.

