#### Exploratory analyses

In an exploratory analysis, interaction terms between group allocation and sex and between group allocation and BMI status will be included in the linear mixed models. Additionally, correlation and regression analyses will be used to evaluate the continuous association between changes in sleep duration and the outcomes.

Two-sided *P*-values ≤ 0.025 will be considered statistically significant for the primary outcomes. For secondary and exploratory outcomes, *P*-values ≤ 0.05 will be considered statistically significant. Statistical analyses will be conducted using IBM SPSS Statistics and R.

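### The learning co-primary outcome is two test scores in one section and one score in another, so whether the alpha split for two outcomes keeps 5% depends on which definition applies

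*Protocol article*

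**What the plan says.** All references are to the protocol article.

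- **Abstract.** Two co-primary outcomes are named: change in BMI z-score and learning ability, from baseline to 12 weeks.
- **Primary outcomes, Learning ability (main study).** "The assessment of learning ability will be performed as motor skill learning and wordlist memory, involving implicit and explicit memory processes". The motor task yields overall 24 h learning, the change in percentage score from the day 1 baseline test to the retention test a day later. The word test yields the number of words, out of 20, recalled after the delay. Immediate motor performance and the non-sequential motor variant are assigned to secondary analyses. Word recall is not.
- **Table 1.** The row for the two tests reads "Learning ability, including skill learning ability and explicit memory".
- **Sample size determination.** The 2.5% two-sided level "was chosen because there are two co-primary outcomes". On learning, "we defined our co-primary outcome as overall 24 h learning". The same paragraph closes by claiming power for learning and memory as a domain.
- **Exploratory analyses.** P-values at or below 0.025 "will be considered statistically significant for the primary outcomes".

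The article gives no composite of the two learning scores, no ranking of them, and no statement that one suffices or that both are needed.

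**The concern.** A reader of the Learning ability section would take both end scores as primary: they stand side by side under that heading, and only other scores are demoted. A reader of the sample size section would take one score, because overall 24 h learning is a term the article attaches to the motor task. These definitions cannot both hold.

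Two things are at stake. The first is the error rate: 0.025 per outcome is the right share for two tests, but not for three separate tests of which any one can carry a primary claim. The second is selection. While the learning measure is unsettled, the score that supports a claim can be picked after results are known. Blinding of outcome assessors and analysts, which the article provides for, does not settle which score is primary.

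**Working it through.** **Inputs from the article.** Two-sided alpha 0.025 per co-primary outcome, 80% power, d = 0.58, 1:1 allocation, 114 completers (57 per arm), 20% dropout and 142 enrolled, all from Sample size determination. The correlation between the two learning test statistics is not given. I assume a range of 0 to 0.9, and take the BMI z-score statistic as independent of both.

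**The plan's own figures.**
- Sample size per arm: n = 2(z₁₋α/₂ + z₁₋β)²/d² = 2(2.241 + 0.842)²/0.58² = 56.5, so 57 per arm and 114 in total. This reproduces.
- Dropout: 114/0.80 = 142.5, against the stated 142. The difference is rounding.
- Alpha: 0.05/2 = 0.025. This is correct for two tests.

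**Reading A: motor 24 h learning is the only learning co-primary (two tests).** The bound is 0.025 + 0.025 = 0.05. If independent, 1 − 0.975² = 0.0494. The 5% level is kept.

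**Reading B: both learning scores are tested at 0.025 and either suffices (three tests).**
- Bound under any dependence: 3 × 0.025 = 0.075.
- If independent: 1 − 0.975³ = 0.0731.
- If the two learning tests are correlated (simulation of normal test statistics, 4 million draws):

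| Assumed correlation | Either learning test | Familywise, with BMI z-score |
|---|---|---|
| 0.3 | 4.8% | 7.2% |
| 0.5 | 4.7% | 7.0% |
| 0.7 | 4.3% | 6.7% |
| 0.9 | 3.6% | 6.0% |

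For learning alone, the either-test error is 1 − 0.975² = 4.9% if independent, against a share of 2.5%.

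**Reading C: one composite, or both learning tests required.** The learning claim uses at most 0.025, so the total is at most 0.05 and the level is kept.

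**Power if both scores stay primary.** Power = Φ(d√(n/2) − z₁₋α/₂), with d√(n/2) = 0.58 × √28.5 = 3.096.
- At 0.025: Φ(3.096 − 2.241) = 80.4%.
- At 0.0125: Φ(3.096 − 2.498) = 72.5%. Total alpha is 0.025 + 0.0125 + 0.0125 = 0.05.

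**The case against.** The strongest reply is that every statement counting the primary outcomes gives two, and that the most explicit definition of the learning outcome is singular. Overall 24 h learning is defined for the motor task, so the plan already has two tests at 0.025 and keeps 5%. Table 1 lists what each instrument yields without marking any outcome as primary. Position under the Primary outcomes heading is not decisive either, since scores meant for secondary analyses are described there too. How two scores are combined is also a detail that a condensed article may leave to the full protocol or analysis plan.

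Much of this stands. A reader might infer that three primary tests will be run and that familywise error is therefore lost. The article does not support that: it nowhere gives word recall its own test at 0.025, and it states no rule that either learning score suffices.

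The conflict itself remains. The Learning ability section opens by making word memory part of the primary outcome, and it demotes other scores by name but not this one. The sample size section defines the outcome by the motor term, yet introduces it as learning and memory and claims power for both. The secondary section Cognitive and academic performance adds to the doubt: it lists delayed memory, but describes none of its named tests as a delayed-memory test. This is disagreement within the article's own text, so an analysis plan that chose one definition would still contradict a section of it.

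**Conclusion.** The learning co-primary outcome is defined inconsistently, and the article's error control holds under some of the definitions but not all. With motor 24 h learning alone, with a single composite, or with both scores required, familywise error stays at or below 5%. If both scores were tested at 0.025 and either sufficed, it would be at most 7.5%: 7.3% under independence, and about 7.2% to 6.0% at assumed correlations of 0.3 to 0.9.

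These excess figures are conditional. They rest on three separate tests, on an either-suffices rule that the article does not state, on a correlation it does not give, and (for the simulated values) on BMI z-score being independent of learning. They show what the ambiguity could cost, not a demonstrated loss of control. The point still needs settling before unblinding, because it decides what counts as success on one of only two primary claims.

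**What to change.** Reconcile the Learning ability section, Table 1 and Sample size determination before unblinding, in one of two ways.

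1. **Preferred: one measure.** Name motor 24 h learning (day 2 delayed retention minus day 1 baseline) as the single learning co-primary outcome, as the sample size section implies, and list 24 h word recall as secondary. Alpha of 0.025 per outcome and the sample size stay as they are. The cost is wording, and word recall loses primary status.
2. **If both scores must stay primary.** Keep 0.025 for BMI z-score and share the learning 0.025 between the two scores, either 0.0125 each or Holm within the pair (the smaller P-value against 0.0125, then the other against 0.025). Total alpha stays at 0.05. The cost is power: at 0.0125, about 72.5% per learning test for d = 0.58 with 57 per arm, against 80.4% at 0.025. Holm recovers some of this for the second score once the first has succeeded.

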#### Secondary outcomes

##### Body fat percentage (main study)

Body fat percentage will be calculated from body composition data (fat mass, soft tissue lean mass, and bone mineral content) obtained by whole-body dual-energy x-ray absorptiometry (DXA; GE Lunar iDXA, GE Healthcare, Madison, Wisconsin, USA).

##### Dietary energy intake (main study)

Dietary energy intake and macronutrient consumption (fat, carbohydrate, and protein) will be estimated using averages of 3 days of diet recording, facilitated through an online dietary assessment tool, myfood24.org, which is available in Danish, English, German, French, Spanish, Norwegian, and Arabic, and has been validated for use with children (43). Children and their parents will be asked to record, in chronological order, all foods and drinks consumed over 3 days of the week. This will exclude Friday, Saturday, and Sunday (44) to align dietary intake with sleep duration during the school days. The parents will receive a MyFood24 link on each registration day. In MyFood24, parents can search for Danish and international food items in the Frida Fooddata database (v2 2017.20.02), the Livmedelsverket National Food Agency database, McCance and Widdowson v7, UK general brands, plus Tesco. The parents will be instructed to record dietary intake either as weighed amounts or using image-based portion sizes. For mixed dishes, parents can create recipes and record the portion consumed. Dietary records will be reviewed by study staff upon return and checked for unrealistic intakes or missing information, which will then be clarified with the parents. If no dietary registration has been completed prior to the visits, parents will be asked to complete a new registration within the following week. In addition, the estimated duration of the daily eating window will be assessed by instructing parents to record the times when their child starts and finishes eating on each registration day.

##### Physical activity and sleep (main study)

Actigraphy will be used to obtain objective measures of daytime physical activity, sleep-wake rhythmicity, and average sleep duration (45). Assessments will be conducted during four monitoring periods of seven days and eight nights each: in the week before visits A, B, and C, and at the midpoint of the active intervention. During each monitoring period, parents will complete daily sleep diaries recording the child's bedtime, estimated lights-off time, and wake-up time.

Actigraphy will be recorded using research-grade, triaxial devices (SOMNOwatch™ eco, SOMNOmedics AG, Germany) worn on the non-dominant wrist (46, 47). Devices will record at 32 Hz, and data will be summarized in 30 s epochs (48). Activity classification, including differentiation between active and sedentary behavior, will be based on movement acceleration, ambient light, and body temperature. Sleep-wake classification will be based on movement thresholds (48).

Lights-off and lights-on times will be recorded manually, either by event marker on the device or in the sleep diary. The sleep period will be defined as the interval between the first and last registered sleep epochs, measured from the registered lights-off to lights-on times. Sleep onset will be defined when movement/activity remains below a predefined threshold for 15 consecutive epochs (7.5 min), after which the full 15-epoch period will be backward-labeled as sleep (48). Wake onset will be defined when movement/activity exceeds the same threshold for four consecutive epochs, after which the full 4-epoch period will be backward-labelled as wake (48).

As the devices are not waterproof, they must be removed during bathing and swimming. Non-wear periods will therefore be expected and will be defined as ≥20 consecutive minutes with no activity detected on an*y* axis (49). Data from a seven-day monitoring period will be considered valid if the participant has at least 4 days of data with at least 16 h of wear time per day (49).

##### Brain activity patterns (main study)

Brain activity patterns will be measured at rest during learning and cognitive performance testing using full-cap, 64-channel electroencephalography (EEG; BioSemi, Netherlands) (50). EEG allows the recording of electrical brain activity through electrodes placed in a cap covering the head. Thus, it is possible to measure very small electrical variations associated with synchronization of neuronal activity. Additionally, electromyographic recordings (EMG; BioSemi, Netherlands) (50) will also be obtained from two hand muscles (m. first dorsal interosseus and m. abductor pollicis brevis) during the motor learning task. EEG measures, which serve as markers of neuroplasticity, will be analyzed for connectivity and overall brain activity, and these neutral measures will be related to behavioral measures of learning.

##### Cognitive and academic performance (main study)

Cognitive performance will be evaluated using standardized computer-based tests of attention, working memory, delayed memory, processing speed, and math and reading comprehension (51). Neuropsychological tests include a computer-based modified Eriksen Flanker Test to evaluate reaction time, response accuracy, and inhibitory control. Additionally, tablet-based working memory and attention tests will be performed using the Cambridge Neuropsychological Test Automated Battery (CANTAB; cambridgecognition.com). These include motor screening (MOT), spatial working memory (SWM), reaction time (RT), Multitasking (MTT), and sustained attention (RVP). Mathematics proficiency and reading comprehension will be evaluated using the Hogrefe Math Test (MGR) and the Hogrefe Danish Reading Comprehension Test, respectively.

##### Energy expenditure (substudy-I)

The resting metabolic rate (RMR) and diet-induced thermogenesis (DIT) will be measured using indirect calorimetry (Vyntus CPX, Intramedic A/S, Denmark). The children will come to the laboratory in the fasted state and breathe normally for 25 min under a transparent plastic hood to measure RMR (52). Subsequently, they will consume a standardized breakfast meal (*t* = 0). To estimate DIT, further assessments of energy expenditure will be conducted 45–70 min and 95–120 min after meal ingestion. The size of the test meal will be identical before and after the intervention for all children. If a child does not consume the entire meal at baseline, the leftovers will be weighed, and the meal will be adjusted accordingly after the intervention. DIT will be calculated as the incremental area under the curve of energy expenditure over time and will be expressed as absolute calories (kcal) and percentage of ingested calories (%) (53). Blood samples (10 mL) will be collected in the fasting state and 2 h after the completion of the meal test.

Total energy expenditure (TEE) will be assessed using doubly labeled water (DLW), that is, water enriched with two stable isotopes of oxygen and hydrogen (^18^O and ^2^H) (54–56). On the first day of visits A and B, the children will provide a baseline urine sample and drink 50 mL of DLW. The first post-DLW urine sample will be collected the following morning, and 6 additional urine samples will be collected at home over the next two weeks. The DLW method is based on the differential rates of 2H and 18O excretion to estimate the rate of carbon dioxide (CO_2_) production (57). CO_2_ is the end product of human oxidative metabolism and is thus a direct metric of energy expenditure under free-living conditions (58).

##### Subjective feelings of hunger and satiety (substudy-I)

Subjective feelings of hunger and satiety will be obtained using an image-adapted 1–5 point rating scale, called “Teddy the bear”, which has been validated for school-aged children (59). The rating scale will be completed in the fasting state, and again at 1 and 2 h after consuming a standardized breakfast meal.

